# Sleep Technology Intervention to Target Cardiometabolic Health (STITCH): a randomized controlled study of a behavioral sleep extension intervention compared to an education control to improve sleep duration, blood pressure, and cardiometabolic health among adults with elevated blood pressure/hypertension

**DOI:** 10.1186/s13063-023-07658-6

**Published:** 2023-10-10

**Keywords:** Sleep, Hypertension (HTN), Systolic blood pressure (SBP), Diastolic blood pressure (DBP), Cardiometabolic disease (CMD), Sleep coaching

## Abstract

**Background:**

Short sleep duration, defined as < 7 h sleep on weeknights, affects 40% of the US adult population, contributing to the increased risk for cardiometabolic diseases, decreased safety, and poorer mental health. Despite the prevalence of short sleep duration, few studies have tested interventions to extend sleep duration. The objective of this study is to test the effects of a behavioral sleep extension intervention on sleep duration, blood pressure, and other measures of cardiometabolic health among adults with elevated blood pressure or hypertension.

**Methods:**

This is a single-blind, randomized controlled trial to determine the impact of a behavioral sleep extension intervention on sleep duration and cardiometabolic health among individuals with short sleep duration (< 7 h per night) and elevated blood pressure or hypertension (SBP 120–150 mmHg or DBP 80–90 mmHg). After completing the screening, participants will be randomly assigned to either a sleep coaching (intervention) or health education (control) group. The participants will have weekly contact for either coaching or education for 8 weeks (intervention period) followed by monthly coaching or education for the next 2 months (maintenance period). Participants will complete assessment visits, actigraphy, and 24-h ambulatory blood pressure recording at baseline/screening, 8 weeks, and 6 and 12 months. The primary outcome is sleep duration at 8 weeks, and the secondary outcome is blood pressure at 8 weeks.

**Discussion:**

The results of this study will determine the effects of behavioral sleep extension on sleep and cardiometabolic health among adults with short sleep duration and elevated BP/hypertension. The results will inform the feasibility and efficacy of behavioral sleep extension and provide information needed for future multi-site effectiveness studies.

**Trial registration:**

ClinicalTrials.gov NCT04766424. Registered on 21 February 2021.

## Introduction

### Background and rationale {6a}

According to data from the National Health Interview Survey,70.1 million US adults (29.2%) sleep < 6 h per 24-h period [1], below the consensus recommendation of “at least 7 h” needed for health and performance among adults [2]. Therefore, a large portion of US adults could potentially improve health and quality of life through extending sleep duration. Meta-analyses demonstrate compelling evidence that short sleep duration independently increases cardiometabolic diseases (CMD) including a 20% increase in hypertension, 40% increase in diabetes22, and 0.23% higher HbA1c in individuals who have type 2 diabetes [3], risk ratios comparable to other lifestyle risk factors such as overweight and physical inactivity. Experiment sleep restriction increases in BP among healthy and hypertensive participants [4, 5], as well as increasing inflammation [6], insulin resistance [7, 8], and caloric intake [9]. Taken together, the studies demonstrate biological and behavioral effects of short sleep duration on CMD development and management.

Despite the well-known negative effects of short sleep duration, surprisingly little attention has been paid to the development of sleep extension interventions and testing whether such treatments can improve CMD. Studies have demonstrated short-term sleep extension results in decreased insulin resistance [10, 11] decreased appetite [12] and lower intake of fat, carbohydrates, and sugars [13]. Together, this growing body of research demonstrates short-term sleep extension is feasible and may confer health benefits for CMD risk factors. However, these studies are limited by small sample size, high staff involvement in the intervention (e.g., intensive coaching and monitoring), and short-term follow-up. Therefore, our project moved this important research forward, taking it from proof-of-concept to efficacy studies to research conducted in more generalizable clinical populations [14].

### Objectives {7}

The goal of this proposed study is to conduct a randomized controlled trial to test the efficacy of our behavioral sleep extension intervention on 24-h ambulatory BP (ABP) and other key biological and behavioral CMD risk factors among participants with short sleep duration and elevated BP/hypertension. The intervention will be completed over a 12-month period in 3 phases, intervention (weeks 0–8), maintenance (months 2–6), and follow-up (months 6–12), allowing us to test the short-term and extended effects of our intervention.Aim 1: To estimate the magnitude of the acute (8 weeks) and extended (12 months) effects of our behavioral sleep extension intervention compared to a health education control group on sleep durationAim 2: To test the effects of our behavioral sleep extension intervention compared with a health education control group on CMD risk factors including 24-h ABP, BMI, body fat, and CMD risk biomarkers (inflammation, glycemic control, lipids)Aim 3: To evaluate the effects of the intervention on key lifestyle behaviors (e.g., diet and physical activity) and patient-reported outcomes (sleep quality, sleepiness quality of life)

### Hypotheses

Compared to the education control group, we predict greater improvements in sleep duration in the intervention group in sleep duration (aim 1), 24-h ABP, and other measures of BP and CMD risk (aim 2) and health behaviors and patient-reported outcomes (aim 3). We predict improvements will persist at the 12-month follow-up, but the effects of the intervention will be attenuated over time.

### Trial design {8}

This is a single-blind, parallel-group, randomized controlled trial with a 1:1 allocation ratio and superiority framework. The study will test a behavioral sleep extension intervention compared to an education control group. The primary endpoint is 8 weeks and the secondary endpoint is 12 months. A CONSORT-style flow chart for the trial is shown in Fig. 1.

**Fig. 1 Fig1:**
[figure not shown]
CONSORT-style flow chart for the trial

## Methods: participants, interventions, and outcomes

### Study setting {9}

This study will recruit participants with elevated BP/stage I hypertension and sleep duration < 7 h from community settings in Salt Lake City, Utah, and the surrounding area.

### Participant timeline {13}

The schedule of time points, study assessments, and interventions is listed in Fig. 2.

**Fig. 2 Fig2:**
[figure not shown]
Schedule of time points, study assessments, and interventions

After web or telephone screening, participants will complete a baseline/screening visit. Participants will undergo standardized BP screening to determine BP eligibility. The BP screening protocol involves 3 unattended BP recordings taken with an automated BP machine (HEM-907HL, OMRON Healthcare Inc.) after a 5-m quiet resting period and 3 m between measurements. If they meet the study criteria, they will review the consent form with the study staff and complete the informed consent prior to continuing the study visit. Participants will complete self-reported questionnaires and cognitive testing and then will wear the study devices at home over the next 10 days (Apnea link monitor for 1 night, ambulatory blood pressure monitor (OnTrak Ambulatory Blood Pressure Monitor 90,227, Spacelabs Inc.) for 24 h, and actigraphy and physical activity monitor for 10 nights). At the end of the baseline period, participants will return to the lab to download their devices and will have their blood drawn. If eligible for the study, they will be randomized to either the sleep extension intervention group or the education control group. They will receive a study letter and materials in the mail, as well as a call from the study coach informing them of their group assignment. The study interventions have 3 main periods. In the intervention period (study weeks 1–8), participants will receive 8-weekly intervention or control sessions and content. In the maintenance period (months 2–6), participants will receive monthly intervention or control sessions and materials. Finally, in months 6–12, participants will be observed, but there will be no interventions delivered.

### Eligibility criteria {10}

The following are the inclusion criteria:Age 18–65 years.In-office BP readings indicating elevated BP/stage I/II hypertension (SBP of 120–150 mmHg or DBP of 80–90 mmHg). Note that participants taking antihypertensive medications will be permitted if stable dose for > 8 weeks and willing to maintain their dose for the 8-week intervention period.Time in bed < 8 h and habitual sleep duration < 7 h via actigraphy at baseline/screening.Smartphone user.Able to read/write English.

The following are the exclusion criteria:High risk or presence of moderate to severe comorbid sleep disorders (i.e., obstructive sleep apnea, restless legs syndrome, or insomnia) as assessed by the questionnaires and overnight obstructive sleep apnea at the baseline/screeningResistant hypertension, defined as currently taking > 4 antihypertensive medications or 3 medications and standardized in lab BP > 130 mmHg SBP or 80 mmHg DBP at screeningHistory of cognitive or neurological disorders (e.g., dementia, Parkinson’s, multiple sclerosis)Arm circumference > 50 cmPresence of major psychiatric disorders (e.g., schizophrenia, bipolar disorder), alcohol abuse on screening questionnaire (women > 7 drinks per week and more than 4 drinks on one occasion; men > 14 drinks in 1 week and more than 5 on one occasion), drug use on the NIDA-Modified ASSIST (score > 3), and moderate to severe depressive symptoms (PHQ-8 > 9)Unstable or serious medical illness that would interfere with participation (cancer, renal disease on dialysis)Overnight work of more than 1 × per monthUse of hypnotic or stimulant medicationsSituations that would significantly impact the ability to extend sleep, including overnight caregiving responsibility for children under the age 1 and elderly or disabled adults > 1 × per weekInability to read or write in EnglishPregnancy/desire to become pregnant during the study periodCurrently following weight loss program, bariatric surgery in the past year, or current use of weight loss medications

### Who will take informed consent? {26a}

Participants will attend a screening visit, and prior to consent, the research staff will take their resting blood pressure using a standardized protocol. Participants who are eligible based on their blood pressure readings will complete informed consent. Consent will be completed by the trained study staff (the research coordinator or research assistant) during an in-person visit to the University of Utah. The informed consent document will be reviewed with participants after a standardized blood pressure reading to determine preliminary eligibility.

### Additional consent provisions for collection and use of participant data and biological specimens {26b}

This study includes blood draws for cardiometabolic risk markers (e.g., lipids, glycated hemoglobin (HbA1c)) as well as Alzheimer’s-related biomarkers (targeted metabolomics, lipidomics) and the genetic risk gene apolipoprotein E4 testing (APOE4). In the consent process, participants will have the opportunity to opt out of blood draws, opt out of genetic testing, and the option to opt out of receiving results of genetic testing.

### Interventions

#### Intervention description {11a}

The behavioral sleep extension intervention consists of a wearable sleep tracker, a weekly educational email, and one weekly phone call from a coach. The maintenance intervention consists of monthly email and phone calls.Self-monitoring (wearable sleep tracker): Participants receive a Fitbit wearable sleep tracker to allow them to monitor their sleep and discuss the results with the coach. Participants and the coach will have access to the sleep tracker data through a dashboard on the Fitabase platform. Participants will be instructed to enter their sleep goals into the sleep tracker app.Education: Participants will receive weekly educational content via email. Topics include the importance of sleep for health (e.g., what is healthy sleep?), regulation of sleep and circadian rhythms, and strategies to avoid bedtime procrastination. The weekly educational content consists of written and video didactic content (e.g., TED talks). Email was selected for the delivery mode to promote engagement, as its use is already integrated into the lives of most people, and it is accessible across platforms (e.g., smartphones, desktops, or tablets). Educational content (Fig. 3) is reinforced in the telephone coaching sessions.Motivational enhancement (telephone coaching): The weekly telephone coaching sessions are used to set goals related to the participant’s sleep, increase commitment to these goals, and problem-solve barriers to achieving the goals. The main behavioral goal is increasing time in bed. The first coaching session will be a 20-min engagement session, which includes introductions, rationale for the program, clarifying the role of the coach, reviewing the participants’ baseline sleep data, setting goals for the program for both sleep and daytime function, and reinforcing the participants’ commitment to change their behavior. In the following coaching sessions, the coach and participant will have a brief (5–10 min weekly) follow-up call to review the progress, boost self-efficacy, problem-solve barriers to progress, and set goals for the following week. During the maintenance period (months 2–6), the calls will be scheduled monthly. In between sessions, the coaches will be available, mostly over email, to troubleshoot any problems with the educational material or sleep tracker. The coaching protocol is based on the principles of Supportive Accountability and uses techniques drawn from cognitive behavioral therapy and motivational interviewing, such as goal setting and developing discrepancies between current and desired behaviors. A list of the intervention and coaching session content is listed in Table 1. Coaches are trained to set collaborative goals, elicit change talk, and include relevant sleep-related research in their sessions (e.g., even an improvement of 20 min can improve your performance).

**Fig. 3 Fig3:**
[figure not shown]
Educational content

**Table 1 Tab1:** Intervention content and coaching

Week	Content	Coaching (min)
1	Intro basics of sleep	20
2	Beat bedtime procrastination	5–10
3	Weekends and challenges	5–10
4	Stress and sleep	5–10
5	The sleep environment	5–10
6	Sleep and the brain	5–10
7	Effects of sleep	5–10
8	Maintaining your gains	5–10

#### Control group description

Participants assigned to the health education control group will be provided with weekly health education emails with content written at < 4th grade level. Participants in this group will also receive brief weekly scripted telephone calls from the coach (< 5 min) to determine if they received the health information and if they had any questions about the materials. Coaches will not provide sleep counseling or goal setting but may clarify terms or concepts. Participants in the control group will be instructed to maintain their current sleep schedule and will not be monitored with sleep diaries, a technique previously reported to produce little change in sleep timing over 4 weeks.

#### Measures of intervention fidelity

All coaching sessions will be recorded for training and fidelity monitoring. All coaches will be trained until they reach a criterion of adherence to the treatment protocol before being assigned study participants. In each quarter, [name] (co-PI) will review approximately 10 sessions quarterly in year 1 and 10 sessions yearly in subsequent years and code them for adherence using previously developed rating scales [15]. Items include aspects of the session content (e.g., eliciting questions or problems about the intervention, setting goals), structure of the session (e.g., sets an agenda), and therapeutic process (e.g., uses open-ended questions, appropriate session pacing). Scores less than 80% will trigger re-training and review of 5 practice sessions for re-approval. Similarly, a random 10% of control sessions will be reviewed using a standardized checklist for the presence of sleep-related content or health advice. If any sleep or health advice is provided, this will trigger re-training.

#### Criteria for discontinuing or modifying allocated interventions {11b}

Participants may be removed from the study if the participant requests withdrawal or the principal investigators consider it necessary to stop the intervention (e.g., significant change that would significantly affect study participations such as pregnancy or a critical injury or major change in health, beginning a shift work job). In this case, the participant would be discontinued from the study, including stopping receiving their emails and coaching sessions. They would receive compensation for study tasks completed up to that point and would not be invited to complete further follow-up assessments. Any information and data collected will be analyzed with the rest of the data.

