#### Plans to promote participant retention and complete follow-up {18b}

Retention for the assessment visits will be handled by the study staff. During informed consent, the staff will discuss with the participants the differences between intervention and assessment as well as the impact of dropout on the validity of study results, while also highlighting voluntary participation. For participants who drop out of the intervention (defined as nonattendance of the coaching or health education calls from that point to the end of the intervention period), we will continue to attempt to obtain outcome assessments. We will respond with empathy and attempt to collect primary outcomes if the full assessment is not feasible. Monetary incentives include payment for each study component and a $40 bonus for the completion of all sleep and ABPM time points.

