### Methods in analysis to handle protocol non-adherence and any statistical methods to handle missing data {20c}

We plan to apply multiple imputation to impute missing outcome data, using comprehensive imputation models that include both non-missing measurements from the variables included in the data analysis as well as additional auxiliary variables that are considered to be predictive either of the risk of missingness or the values of the variables whose missing values are being imputed. The multiple imputation approach has been established as superior to alternatives, including complete case analysis or simplified ad hoc single imputation approaches [39, 40].

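### When the investigators stop the intervention, outcome assessment stops too, which conflicts with the retention section for weeks 1–8 and creates avoidable missing outcomes

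*Protocol article*

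**What the plan says.** Three sections of the protocol article bear on this point.

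- **Discontinuation {11b}.** Removal from the study is possible "if the participant requests withdrawal or the principal investigators consider it necessary to stop the intervention". The examples given are changes "such as pregnancy or a critical injury or major change in health, beginning a shift work job". Emails and coaching then cease, and the section continues: "They would receive compensation for study tasks completed up to that point and would not be invited to complete further follow-up assessments". Data already in hand are kept: "Any information and data collected will be analyzed with the rest of the data".
- **Retention {18b}.** For participants who drop out of the intervention, "we will continue to attempt to obtain outcome assessments". Dropout is "defined as nonattendance of the coaching or health education calls from that point to the end of the intervention period". No reason for the nonattendance is specified. The section also allows for collecting the primary outcomes alone when a full assessment cannot be done, and has staff explain at consent that intervention and assessment are different things.
- **Missing data {20c}.** "We plan to apply multiple imputation to impute missing outcome data, using comprehensive imputation models" that also draw on auxiliary variables.

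**The concern.** Section {11b} joins two events that a trial should keep apart. One is a participant's wish to leave the study. The other is a decision by the investigators that the intervention should not go on. The second need not end measurement, because the person has not asked to stop being assessed. Under {11b} it does.

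The example reasons are post-randomisation events that plausibly change sleep or blood pressure: new shift work, pregnancy, serious injury, a major health change. Outcomes would therefore go missing, by rule, for reasons that may be related to the outcome. Section {18b} takes the opposite approach for people who stop attending calls, and the two groups overlap. At stake are the as-randomised comparison of sleep duration and 24-hour SBP, and some of the attrition allowance in the sample size. Data never collected cannot be restored by any analysis plan.

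**Working it through.** **1. The two rules side by side.** Take a participant whose intervention the principal investigators stop in week 4.

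- Under {11b}: discontinued from the study and not invited to the 8-week, 6-month or 12-month assessments.
- Under {18b}: attends no calls from week 4 to the end of the intervention period, so meets the definition of intervention dropout. Staff keep trying to obtain outcomes.

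Staff cannot follow both.

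**2. How far the conflict reaches.** The participant timeline puts the intervention period at weeks 1–8, the maintenance period at months 2–6, and no intervention in months 6–12. The {18b} definition runs only to the end of the intervention period. A stop in the maintenance period is outside it, so there is no direct contradiction. Such a stop still costs later assessments but cannot affect the 8-week primary outcome. In months 6–12 there is no intervention left to stop.

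**3. The plan's own sample size.** Inputs from Sample size {14}: SD of change 37.4 min, correlation 0.75, attrition 20%, effect 20.2 min, two-sided alpha 0.05, 80% power.

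- ANCOVA residual SD = 37.4 × √((1 + 0.75)/2) = 34.98 min.
- This requires 48 complete participants per arm (normal approximation), and 48/0.80 = 60 per arm, 120 in total. The stated figure reproduces.
- Power at 48 per arm is 80.7% by the normal approximation and 79.9% by the noncentral t.
- For SBP, residual SD = 11.8 × √(1 − 0.70²) = 8.43 mmHg, which with 4.86 mmHg again gives 48, then 60, per arm.

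The sample size is not at fault, but it has no slack beyond the 12 losses per arm (20% of 60).

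**4. Possible bias.** The documents give no stopping rates and no outcomes after stopping. Everything in this step is assumed. The target is the comparison of everyone as randomised, whether or not the intervention continued. Let f_T and f_C be the proportions of the coached and control arms stopped with no 8-week measurement.

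- *Lost effect imputed as kept.* Only the coached arm has an effect to lose. If stopped participants truly have none but are imputed with all of it, overstatement = f_T × 20.2. At 5% (3 of 60) this is 0.05 × 20.2 = 1.0 min. At 10% (6 of 60) it is 0.10 × 20.2 = 2.0 min. This arises even when the arms are stopped equally.
- *Event shifts sleep itself.* If imputed sleep exceeds true sleep by a common d in both arms, bias = (f_T − f_C) × d. At equal rates it is 0. At 5% against 0% with d = 20 to 60 min it is 1.0 to 3.0 min. At 10% against 0% it is 2.0 to 6.0 min. More stops among controls would reverse the sign.

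**5. Cost in power (sleep, t-based, ANCOVA residual SD 34.98 min).**

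| Total attrition | Complete per arm | Detectable effect at 80% power | Power at 20.2 min |
|---|---|---|---|
| 10% | 54 | 19.0 min | 84.4% |
| 15% | 51 | 19.6 min | 82.3% |
| 20% | 48 | 20.2 min | 79.9% |
| 25% | 45 | 20.9 min | 77.3% |

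Stopping 5% of each arm without follow-up uses 3 of the 12 allowed losses per arm. If other causes already used all 12, power would fall to 77.3%.

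**The case against.** The two sections can be read as covering different people: {11b} those removed from the study, {18b} those who merely stop attending. Removal is discretionary, and ending contact is proper when a participant fully withdraws. This stands in part. It narrows the conflict to investigator stops in weeks 1–8, but nothing in {18b} excludes those people from its definition.

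A reader might go further than the documents allow in four ways.

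- **That multiple imputation cannot repair the loss.** Imputation is valid if data are missing at random given what is observed. Section {20c} includes auxiliary variables, data up to the stop are kept, and dropouts followed under {18b} supply some off-intervention outcomes. The supportable statement is weaker: with no post-stop data, the assumption is untestable for these participants, and their imputed values may reflect continued treatment. A sensitivity analysis may be in a SAP that is not shown.
- **That unblinded coaches drive removal, and more so in the coached arm.** Section {11b} gives the decision to the principal investigators. One of them oversees the coaching, but that role includes fidelity review in both groups. Both arms have weekly and then monthly sessions. Coached calls are longer (20 min, then 5–10 min, against under 5 min) and coaches see tracker data, so unequal detection is conceivable. The documents do not show it.
- **That the effect is overstated by a known, large amount.** The larger figures need unequal removal and a large sleep shortfall, neither of which has a source in the documents.
- **That every such loss affects the primary outcome.** Only stops before the 8-week assessment can.

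**Conclusion.** The point holds in a limited form. As written, {11b} ends assessment for participants who have not asked to leave, for reasons plausibly related to sleep and blood pressure. For investigator stops in weeks 1–8 it conflicts directly with {18b}. For later stops it is a design weakness that touches only the 6- and 12-month outcomes.

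The size and direction of bias are unknown. The illustrative overstatement of about 1.0 to 2.0 min against a 20.2-min target assumes that 5% to 10% of the coached arm is stopped before week 8, that those people have no effect at all, and that imputation gives them the whole effect. If part of the effect persists, or the auxiliary variables capture the change, the figure is smaller. The use of the attrition allowance follows from any such loss. This should be fixed, but it does not by itself invalidate the primary analysis.

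**What to change.** Leave the decision on when to stop the intervention as it is, and amend only what follows from it:

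- In {11b}, separate stopping the intervention from withdrawing consent to follow-up.
- Keep inviting participants whose intervention is stopped to the scheduled actigraphy and ABPM assessments at 8 weeks, 6 months and 12 months, or at least collect the primary outcomes as {18b} already allows. Analyse them as randomised.
- End contact only for those who withdraw consent to follow-up.
- Record the reason, date and arm of every stop, so that rates can be compared between arms.
- Reconcile {11b} and {18b} so that each participant falls under one follow-up rule.

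The cost is a short amendment and a few more assessments. These visits are already in the schedule for every participant, although the documents show no budget. Some of the added measurements will reflect the intercurrent event as well as the allocated group. That is what an as-randomised comparison accepts, and the separate per-protocol analysis in {20b} remains for participants who attended all sessions.
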